# Verum versus sham tDCS in the treatment of stroke-induced apraxia: study protocol of the randomized controlled trial RAdiCS -“Rehabilitating (stroke-induced) Apraxia with direct Current Stimulation”

**DOI:** 10.1186/s42466-020-0052-y

**Published:** 2020-03-04

**Keywords:** Anodal transcranial direct current stimulation (tDCS), (Limb) apraxia, Randomized controlled trial (RCT), Two-arm parallel intervention, Stroke, Rehabilitation, Activities of daily living, Cologne Apraxia Screening (KAS)

## Abstract

**Introduction:**

Stroke is the leading cause of acquired disability in western societies. (Motor) cognitive deficits like apraxia significantly contribute to disability after stroke, harming activities of daily living and rehabilitation outcome. To date, efficient therapeutic options for apraxia remain sparse. Thus, randomized controlled trials (RCTs) are warranted.

**Methods:**

Based on promising results of a pilot study, the on-going RAdiCS (**R**ehabilitating stroke-induced **A**praxia with **di**rect **C**urrent **S**timulation) study is a randomized controlled trial, which follows a double-blinded (investigator and patient), two-arm parallel interventional model. It is designed to include 110 apraxic patients (as diagnosed by the Cologne Apraxia Screening, KAS) in the subacute phase after a left hemisphere (LH) stroke. The University of Cologne initiated the trial, which is conducted in two German Neurorehabilitation Centers.

The study aims to evaluate the effect of anodal (versus sham) transcranial direct current stimulation (tDCS) applied over the left posterior parietal cortex (PPC) with an intensity of 2 mA for 10 min on five consecutive days on apraxic deficits. In addition to anodal or sham tDCS, all LH stroke patients undergo a motor (cognitive) training that is performed before and after the stimulation (off-line stimulation).

The primary outcome measure is the (differential) change in the overall KAS score after five daily sessions of anodal versus sham tDCS when compared to the baseline assessment before tDCS. Secondary study outcomes include further apraxia scores, aphasia severity, and measures of motor performance and disability after stroke. All outcome measures are obtained in the post-stimulation assessment as well as during follow-up (3–4 months after tDCS).

**Perspective:**

The RCT RAdiCS shall evaluate in a large number of LH stroke patients whether anodal tDCS (compared to sham tDCS) expedites the rehabilitation of apraxia – over and above additional motor (cognitive) training and standard care. A positive study outcome would provide a new strategy for the treatment of apraxia, which hopefully ameliorates the negative impact of apraxia on daily living and long-term outcome.

**Trial registration:**

Clinical Trials Gov: NCT03185234, registered 14 June 2017 ; Deutsches Register für Klinische Studien: DRKS00012292, registered 01 June 2017.

**Trial status:**

Participant enrollment began on 22 June 2017. The trial is expected to be completed on 30 June 2022.

## Introduction

Stroke is the leading cause of acquired disability in Western societies. Besides primary sensorimotor impairments, cognitive deficits significantly contribute to stroke-related disability. One of those stroke-related (motor) cognitive deficits is apraxia, the “inability to perform specific and predefined actions or to carry out learned and purposeful movements, independently of sensory, motor and (other) cognitive deficits” [14]. Apraxia mainly occurs after a left hemisphere (LH) stroke, with prevalence rates ranging from 30 to 50% [8].

Apraxia may affect different body parts: While limb apraxia involves the hand and the arm, bucco-facial apraxia affects movements and gestures of the face. Apraxia can impair three different motor domains: (i) imitation of (meaningless/meaningful) gestures, (ii) pantomiming the use of objects/tools, and (iii) actual tool use [14]. Notably, apraxic impairments affect both (the contralesional and the ipsilesional) hands.

Apraxia negatively impacts activities of daily living (ADLs [16];). Moreover, apraxic stroke patients show an increased dependency on a caregiver’s assistance and return less frequently to work than patients without apraxia [11]. Thus, apraxia is a poor prognostic factor for the rehabilitation outcome after stroke, calling for the development of novel, efficient therapies. To date, specific therapeutic options for apraxia remain sparse [8]. So far, only two (behavioral) treatment strategies for apraxia have been investigated by randomized controlled trials: gesture training (*n* = 33 [16];) and strategy training (*n* = 113 [7];). Moreover, the evidence for the effectiveness of specific therapeutic strategies for apraxia after stroke is deficient [20].

Recently, the potential of non-invasive brain stimulation, such as transcranial direct current stimulation (tDCS) for the rehabilitation of specific stroke-induced deficits has been recognized (for an overview see [13]). TDCS is a well-tolerated and safe method [2, 4], which modulates neuroplasticity in the human brain by the application of weak currents inducing local effects and effects on connected remote areas [15].

In post-stroke rehabilitation, tDCS was shown to enhance motor and language functions [9] or to ameliorate symptoms of visuospatial neglect [17]. However, up to date, due to a lack of (large) randomized controlled trials (RCTs), there is no Level A recommendation (definitive efficacy) for tDCS in post-stroke rehabilitation for any specific indication [13]. For apraxia, studies in healthy subjects [18], apraxic stroke patients [1, 5], and patients with cortico-basal syndrome [3] showed an improvement in (hand) gesture processing and imitation by anodal tDCS over the left posterior parietal cortex (PPC).

## Methods

### Aim of the trial

A randomized controlled trial (RCT) on the utility of tDCS in apraxia is still missing. Thus, the RCT RAdiCS (Rehabilitating stroke-induced Apraxia with direct Current Stimulation) aims to investigate whether (in addition to motor (cognitive) training) repetitive anodal tDCS applied above the left, ipsilesional PPC can facilitate the recovery of the motor cognitive deficit apraxia during neurorehabilitation in the subacute to chronic phase after LH stroke.

### Study description and study design

This multicenter study is an investigator-initiated, prospective randomized controlled trial (RCT) and follows a double-blinded (patient and investigator) study design with a parallel two-arm interventional model. As an intervention, we apply tDCS with CE-certified DC-Stimulators (NeuroConn, Ilmenau, Germany). In the context of motor rehabilitation after stroke, the clinical trial adheres to the German medical device law (Medizin-Produkte Gesetz, MPG; §23b).

We assume that the verum stimulation (anodal tDCS over the left parietal lobe) leads to a more significant improvement in apraxia severity than sham stimulation [1]. The primary endpoint is the difference in the total score of the Cologne Apraxia Screening (KAS [19]) between the post-interventional investigation and baseline. Thus, the null and alternative hypotheses are:
**H**_**0**_**:** The change of the motor-cognitive apraxic deficits (as assessed by the KAS) between the baseline assessment and the post-interventional assessment is the same in both treatment groups (verum tDCS and sham tDCS).**H**_**1**_**:** The change of the motor-cognitive apraxic deficits (as assessed by the KAS) between the baseline assessment and the post-interventional assessment is different in the verum tDCS group than in the sham tDCS group.

A pilot study following the identical interventional and training procedure was performed before this RCT [1]. Here, 20 apraxic patients showed a standard deviation (SD) of about 7 points in the comparison of the KAS-score between baseline and post-interventional assessment. The difference between the sham- and the verum-interventional group was 4.6 points. Based upon these data, a sample size of 50 per study arm is required to ensure a difference in effect of 4 points at an SD of 7 in a two-sample t-test at a level of significance of 0.05 and a power of 0.8. We added 10% for eventual non-parametric testing, leading to 55 patients per study arm or a total of 110 patients in the intention-to-treat (ITT) collective. Additional participants replace drop-outs that do not fulfill the ITT-criteria (i.e., drop-out before first stimulation).

The primary collective for the analyses is the ITT collective, including all patients with the baseline KAS-score and the application of at least one stimulation. The secondary per-protocol (PP) collective includes all patients with a baseline and post-interventional KAS-score, plus the application of the verum or sham intervention according to the protocol, with the possibility of missing one stimulation, i.e., at least 4/5 stimulations must have been completed. The descriptive analysis will be conducted for the entire study cohort and both study groups. Two-sided statistical tests will be performed with the level of significance set to 0.05. The analysis of effectiveness will primarily be carried out in the ITT population “as randomized”. The PP population (at least 4/5 stimulations received) will be assessed for the sensitivity analysis. The analysis of safety will be conducted in the population “as treated” (at least 1/5 stimulations received).

Including screening, nine study visits are scheduled, eight of which are handled during the inpatient treatment in the neurological rehabilitation centers. The final, ninth (follow-up) visit can also take place at the patient’s home.

The primary outcome measures are collected at three time points: (1) baseline, i.e., in the week before stimulation, (2) post-intervention, i.e., in the week after stimulation, (3) follow-up, i.e., about three to four months after the stimulation. If patients assent, the neuropsychological and motor tests are recorded on video and re-evaluated for interrater-reliability. Please see the study flow chart Fig. 1 and Table 1 for the time points of the scheduled study visits and the respective motor and neuropsychological tests.

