### Outcome measures

The primary outcome measure is the change of the total score of the Cologne Apraxia Screening (KAS [19];) achieved post-interventionally, compared to the patient’s baseline performance. The KAS is a reliable and valid screening tool [8], assessing bucco-facial and limb apraxia with two types of tasks (pantomime of tool use and imitation). The primary analysis is the comparison of the difference in the KAS-score changes between the two study arms (verum vs. sham stimulation) with a t-test in the ITT collective. If necessary, equivalent non-parametric methods are applied. The differences in KAS-score changes between follow-up and post-interventional assessments, as well as between follow-up and baseline assessments, are compared to evaluate a long-term effect. An analysis of variance (ANOVA) with the factor treatment and the co-factors age, KAS-score classification at baseline, and study site will investigate potential influences of the randomization strata on the treatment effect.

Secondary outcome measures are the changes in the additional neuropsychological and motor tests. Further apraxia assessments include the De Renzi test of actual object-use, the De Renzi imitation test, as well as the Goldenberg hand- and finger-imitation test. Moreover, aphasia is assessed by the short version of the Aphasia Check List (ACL-K). For general motor performance, the force of hand extension is assessed bimanually with the Medical Research Council (MRC) paresis scale, and the grip force is measured with a Vigorimeter (Martin Vigorimeter, medium-sized ball). Furthermore, the Action Research Arm Test (ARAT) is applied to both hands, and the Jebsen Taylor Hand Function Test (JTHFT) is applied to the ipsilesional (left) hand. To document the overall disability after stroke, we use the modified Ranking Scale (mRS).

As (cognitive) motor training, the ARAT, the De Renzi Imitation Test, and JTHFT are conducted before and after the stimulation sessions on the five interventional study visits (S1-S5 = T2-T6).

Additionally, the National Institutes of Health Stroke Scale (NIHSS), the Edinburgh Handedness Inventory (EHI), the Hospital Anxiety and Depression Scale (HADS), and the educational background are assessed at study inclusion.

Secondary outcome measures are assessed at the same time points as the primary outcome measures, i.e., at baseline, post-intervention, and follow-up, and are analyzed analogously to the primary outcome measures (see above).

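### The ITT set admits patients without a post-interventional KAS, whom the named primary t-test on change cannot use and the per-protocol sensitivity set excludes

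*Protocol article*

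**What the plan says.** All statements are in the protocol article, Methods.

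- **Primary set** (Study description and study design): the "ITT collective, including all patients with the baseline KAS-score and the application of at least one stimulation".
- **Primary test** (Outcome measures): the "comparison of the difference in the KAS-score changes between the two study arms (verum vs. sham stimulation) with a t-test in the ITT collective". Non-parametric equivalents are held in reserve.
- **Sensitivity set** (Study description and study design): the per-protocol collective "includes all patients with a baseline and post-interventional KAS-score" and at least four of the five stimulations. Its role is stated as: "The PP population (at least 4/5 stimulations received) will be assessed for the sensitivity analysis". No other sensitivity analysis is named.
- **Sample size** (same section): 50 per arm for a "difference in effect of 4 points at an SD of 7 in a two-sample t-test at a level of significance of 0.05" and 80% power. Then: "We added 10% for eventual non-parametric testing, leading to 55 patients per study arm". The resulting 110 is given as the size of the ITT collective. Only patients lost before their first stimulation are replaced.
- **Schedule** (Table 1): KAS at T0, T7 and T8, with no restriction of T7 to patients who completed the course.

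**The concern.** Consider a patient who has a baseline KAS, receives one session and has no KAS at T7. This patient is in the ITT set, counts towards the 110 and is not replaced. The primary endpoint, KAS at T7 minus KAS at baseline, does not exist for this patient. A t-test on that change has nothing to work with unless another rule provides a value.

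The sensitivity analysis does not help. Per-protocol membership requires the T7 score, so the same patient is absent from it by definition. Agreement between the two results would say something about adherence and nothing about missing outcomes.

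The sole primary comparison is at stake. If the reason for a missing T7 score is related to tolerability or perceived benefit, and this differs between arms, a contrast among patients with scores need not equal the as-randomized contrast it is meant to represent.

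**Working it through.** **Inputs from the article:** difference 4 points, SD 7, two-sided alpha 0.05, power 0.80, 1:1 allocation, 10% added for non-parametric testing.

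**1. Reproducing the stated size.**
- Normal approximation: n per arm = 2 × (1.960 + 0.842)² × (7/4)² = 2 × 7.85 × 3.0625 ≈ 48.1, so 49.
- Exact noncentral t: 49.05, so 50.
- 50 × 1.10 = 55 per arm, and 2 × 55 = 110. The stated figures reproduce.

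**2. Who has what the analyses need.**

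| Patient with a baseline KAS and at least one stimulation | In ITT | Change score exists | Can be in PP |
|---|---|---|---|
| T7 KAS present, 4–5 stimulations | yes | yes | yes |
| T7 KAS present, 1–3 stimulations | yes | yes | no |
| T7 KAS absent | yes | no | no |

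The third row is the gap. The patient is in the primary set, is unusable by the named test as it stands, and is invisible to the only named sensitivity set.

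**3. Power if some T7 scores are missing.** The article gives no rate, so 0–20% is an assumption. Evaluable n per arm = 55 × (1 − m). Power is exact t with d = 4/7. The rank-test column multiplies n by 0.955, the large-sample efficiency under normality. The last column divides n by 1.1, as if the whole 10% were needed for the non-parametric test.

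| Missing (m) | n per arm | t-test | Rank test, 0.955 | Full 10% used |
|---|---|---|---|---|
| 0% | 55 | 84.4% | 82.7% | 80.8% |
| 5% | 52.25 | 82.5% | 80.7% | 78.7% |
| 10% | 49.5 | 80.4% | 78.5% | 76.5% |
| 15% | 46.75 | 78.0% | 76.1% | 74.0% |
| 20% | 44 | 75.5% | 73.5% | 71.4% |

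The t-test has 80.8% power with 50 per arm (5 of 55 missing, 9.1%) and 79.96% with 49. It therefore keeps its 80% up to about 10% missing.

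**4. Illustration of bias (constructed, not from the article).** Suppose 10% of the verum arm alone lack T7 and their change would have been 5 points worse than that of the other verum patients. The contrast among patients with scores is then too high by 0.10 × 5 = 0.5 points, or 0.5/4 = 12.5% of the target difference.

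**5. What a longitudinal model can recover.** A patient missing T7 but seen at T8 contributes through the correlation between T8 and T7. A patient with baseline only helps to estimate the common baseline mean and adds little to the T7 contrast. For patients with both scores, and assuming equal variances at T0 and T7 with correlation ρ, the variance relative to a change score is (1 − ρ²) / [2(1 − ρ)] = (1 + ρ)/2. This is never above 1, so adjusting for baseline costs no precision in large samples.

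**The case against.** The strongest reply is that a condensed article leaves missing-data handling to the full protocol or SAP, neither of which is shown. Requiring the post-interventional score for per-protocol and not for ITT suggests that the authors meant to keep such patients. A t-test can be run on imputed changes. This stands against one tempting inference, that every planned analysis is a complete-case analysis. The article states no exclusion rule and no imputation rule. Moreover, the follow-up-minus-baseline comparison needs T8 rather than T7, and the safety analysis needs no KAS at all.

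A reader might also infer that 80% power holds only if every stimulated patient returns a T7 score. The table above contradicts this for the t-test (about 10% missing) and for the rank test at 0.955 efficiency (80.7% at 5%). It is nearly true only if the full 10% is consumed by non-parametric testing. At the lower-bound efficiency of 0.864, power is already 78.7% with nobody missing, so that shortfall is not due to missing scores.

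Loss before T7 should also be low. Eight of nine visits are inpatient, T7 falls in the week after the course, patients and investigators are blinded, and nothing says that a patient who stops stimulation skips T7. All of this stands and limits the size of the problem.

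Per-protocol is a conventional check on adherence, and that is a fair use of it. As the only named sensitivity set, however, it leaves missing outcomes unexamined. The mismatch between the stated set and the stated test also remains.

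**Conclusion.** The point holds as a mismatch between choices the article itself fixes: a primary set that does not require the outcome, a primary test that does, and a sensitivity set that removes the patients in question. The absence of an imputation rule from the article is not the finding.

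No power shortfall is demonstrated. The 110 names no allowance for loss after the first stimulation, but the t-test has enough slack for about 10% missing, given a difference of 4 and an SD of 7. The possible bias cannot be sized from the article. The 0.5-point example rests wholly on assumed one-sided loss and an assumed 5-point deficit. The consequence is probably small, but it concerns the only primary comparison and the data needed for a better analysis are already scheduled.

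**What to change.** - **Primary analysis:** a constrained longitudinal model of KAS at T0, T7 and T8, with a common baseline mean for the two arms and age group and site as covariates. Baseline severity enters through the T0 score itself. The T7 treatment contrast is the estimate. This draws on baseline and T8 information for patients missing T7.
- **Sensitivity analysis:** keep per-protocol for adherence and add a delta-adjusted analysis in which missing T7 scores are made progressively worse, including differently by arm, until the conclusion changes. This matters most for patients with baseline only, for whom the model has little to work with.
- **Data collection:** state that the T7 KAS is sought from every ITT patient, whatever the number of stimulations received.

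The cost is slightly more modelling and a change to the named primary test, which must be fixed and documented before unblinding. The change-score t-test, or its non-parametric equivalent, can stay as a supportive analysis. No new visits or instruments are needed.

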**Fig. 1 Fig1:**
[figure not shown]
RAdiCS study flowchart. *will be escalated for drop-outs who did not receive a stimulation. Abbreviations: KAS=Kölner Apraxie Screening (Cologne Apraxia Screening), ACL-K=Short version of the Aphasia Check List, HADS=Hospital Anxiety and Depression Scale, MRC = Medical Research Council, mRS = modified Rankin Scale, NIHSS=National Institutes of Health Stroke Scale, ARAT = Action Research Arm Test, JTHFT = Jebsen Taylor Hand Function Test. For a list of the applied tests at a given time point, please, see Table 1

**Table 1 Tab1:** List of applied tests at a given time point (T0-T8)

			Stimulation						
			S1	S2	S3	S4	S5		
Time point	T0	T1	T2	T3	T4	T5	T6	T7	T8
Method									
Edinburgh Handedness Inventory (EHI)	X								
Hospital Anxiety and Depression Scale (HADS)	X								
Aphasia Check List - Short version (ACL-K)	X							X	X
Cologne Apraxia Screening (KAS)	X							X	X
National Institutes of Health Stroke Scale (NIHSS)		X							
Goldenberg hand- and finger-imitation test		X						X	X
De Renzi test of actual object-use		X						X	X
De Renzi imitation test			XX	XX	XX	XX	XX		X
Action Research Arm Test (ARAT)			XX	XX	XX	XX	XX		X
Jebsen Taylor Hand Function Test (JTHFT)		4X	XX	XX	XX	XX	XX		4X
Modified Rankin Scale (mRS)		X						X	X
Medical Research Council (MRC)		X						X	X
Vigorimeter (for grip force)		X						X	X

T0 = Screening, T1 = Baseline assessment, T2-T6 = assessments at the stimulation sessions (S1-S5), T7 = Post-interventional assessment, T8 = Follow-up assessment

X = single application of the test, XX = application before and after the stimulation (verum or sham tDCS), 4X = 3 times of training and measurement of the 4th trial

### Arms and interventions

After inclusion in the study, participants are randomized in the proportion 1:1 to both study arms, following a stratification by KAS-Score (i.e., apraxia severity; < 68 / ≥ 68 points), age (< 65 / ≥65 years), and site of investigation (Rehabilitationszentrum Godeshoehe e.V., Bonn / MediClin Fachklinik Rhein/Ruhr, Essen).

In the experimental group, anodal tDCS at an intensity of 2 mA is applied for 10 min on five consecutive days. The anodal rubber electrode (size: 5x7cm, 35cm^2^) is placed over the left PPC at position P3 of the 10/20 EEG system, the reference electrode (size: 5x10cm, 50cm^2^) is located supraorbitally on the right forehead. Electrodes are inserted into sponges and dampened with a saline solution to optimize electrode-skin-interface. To fix the electrodes, a rubber band is placed around the head in addition to the EEG cap.

To avoid sudden current changes, a fade-in and fade-out phase is applied, in which the current increases/decreases. Following the recommendation of the NeuroConn company, we ensured that the change of current is less than 0.5 mA per second. Therefore, we used fade-in and fade-out periods of 6 s duration each, resulting in a change of current of 0.5 mA/1.5 s (= 0.333 mA/s, see Fig. 2). During the stimulation, the patient is instructed to sit relaxed in a chair with eyes either closed or opened, without falling asleep (offline-stimulation).

